### Standard care

Perioperative management other than the pneumoperitoneum strategy is suggested to follow the Spanish Enhanced Recovery Pathways recommendations (detailed in Additional file 3) [26]. Continuous intraoperative neuromuscular monitoring with acceleromyography (TOF-Watch-SX™, Organon Teknika, Oss, The Netherlands) is used. At the end of surgery, the neuromuscular blockade will be fully reversed to a TOF ratio (TOFr) of at least 0.9 before tracheal extubation. An electronic CO_2_ insufflator (Endoflator™, Karl Storz, Tuttlingen, Germany) will be used for gas insufflation into the abdominal cavity through a paraumbilically placed laparoscopic trocar/Veress needle.

Patients in both groups will be ventilated in a volume-controlled ventilation mode, using a tidal volume of 8 ml/kg predicted ideal body weight, with a 20% inspiratory pause time, and positive end-expiratory pressure set at 5 or 10 mmHg in patients with a body mass index (BMI) < 30 or ≥ 30 kg∙m^− 2^, respectively. Oxygen inspiratory fraction is 0.8 throughout surgery. Respiratory rate is set at 12–15 breaths per minute to maintain normal end-tidal CO_2_ values [27].

### Primary outcome

The primary outcome is the recovery of the PQRS at postoperative day 1 (POD1) (see the subsequent sections for details).

### Secondary outcomes

Secondary outcomes include recovery of PQRS at 15 min (T15) and at 40 min (T40) after arrival in the post anaesthesia care unit (PACU) and in the surgical wards during the morning at postoperative day 3 (POD3). Other secondary clinical outcomes include daily postoperative complications until hospital discharge and at postoperative day 28, hospital length of stay (LOS) and secondary process-related outcomes that include the highest IAP level and IAV at which surgery could be performed, hepatic perfusion during pneumoperitoneum and the ventilatory parameters plateau pressure and driving pressure.

Occurrences of diaphragm and abdominal wall contractions or spontaneous breathing efforts and coughing during surgery are collected and compared between the two study groups.

### Substudies

The IPPCollapse-II study has three substudies (see the detailed description in Additional file 4):Levels of biomarkers (neutrophil-lymphocyte ratio, C-reactive protein, interleukin-6 and procalcitonin) are measured in peripheral venous blood samples obtained before surgery and at POD1 and POD3 and compared between the two study groups. For this substudy, blood samples are obtained in all participating centres.Untargeted metabolomic analysis is performed on peripheral venous blood samples and peritoneal tissue, both obtained after initial insufflation of pneumoperitoneum and at the end of the procedure. This substudy includes the first 10 patients in the Hospital Universitari i Politècnic La Fe, Valencia, Spain.Plasma disappearance rate of indocyanine green (PDR_ICG_) after intravenous ICG injection is measured to evaluate hepatic perfusion during pneumoperitoneum as a marker of liver function [28]. This substudy runs only at the University Hospital Gregorio Marañon, Madrid, Spain.

### Post-operative Quality of Recovery Scale

The PQRS is a validated multidimensional PRO tool [29–31] designed to assess patients’ recovery to baseline status in the postoperative period (www.postopqrs.com). In every patient a baseline measurement of PQRS is performed prior to surgery. After surgery, the measurement of the PQRS is repeated at 15 min (T15) and at 40 min (T40) after arrival in the PACU, as well as in the ward on the morning of POD1 and POD3. The PQRS is a verbal survey tool that depicts recovery in the following five domains: physiologic, nociceptive, emotive, functional, cognitive, and also collects overall patient perspective. Each of these domains is assessed with multiple items on an ordinal scale and compared with baseline to evaluate recovery (see Table 2 for details). Recovery is a dichotomised outcome defined by a return to at least baseline values or better at each of the postoperative measurement time points. Overall recovery requires recovery in all domains being assessed, and failure in any domain results in failure of overall recovery.

**Table 2 Tab2:** Post-operative Quality of Recovery Scale (PQRS)

Domain	Variable	Score	Baseline	T15	T40	POD1	POD3
Physiologic	Blood pressure	1–3	+	+	+	+	+
Physiologic	Heart rate	1–3	+	+	+	+	+
Physiologic	Temperature	1–3	+	+	+	+	+
Physiologic	Respiration	1–3	+	+	+	+	+
Physiologic	SpO2	1–3	+	+	+	+	+
Physiologic	Airway	1–3	+	+	+	+	+
Physiologic	Agitation	1–3	+	+	+	+	+
Physiologic	Consciousness	1–3	+	+	+	+	+
Physiologic	Activity on command	1–3	+	+	+	+	+
Nociceptive	Pain	1–5 Likert	+	+	+	+	+
Nociceptive	PONV	1–5 Likert	+	+	+	+	+
Emotional	Sadness/depression	1–5 Likert	+	+	+	+	+
Emotional	Anxiety/nervousness	1–5 Likert	+	+	+	+	+
Functional	Stand	1–3	+	–	–	+	+
Functional	Walk	1–3	+	–	–	+	+
Functional	Eat/drink	1–3	+	–	–	+	+
Functional	Get dressed	1–3	+	–	–	+	+
Cognitive	Name, city and DOB	TF 0	+	–	–	+	+
Cognitive	Numbers forward	TF 2	+	–	–	+	+
Cognitive	Numbers backwards	TF 1	+	–	–	+	+
Cognitive	Word task: list	TF 3	+	–	–	+	+
Cognitive	Executive memory	TF 3	+	–	–	+	+
Overall patient perspective	Ability to work	1–5	–	–	–	–	+
Overall patient perspective	Ability to perform ADLs	1–5	–	–	–	–	+
Overall patient perspective	Clarity of thought	1–5	–	–	–	–	+
Overall patient perspective	Satisfaction anaesthesia care	1–5	–	–	–	–	+

Online scale to assess multiple domains of postoperative recovery over time. Timeline: T15–15 min in PACU, T40–40 min in PACU Scoring: Physiologic 1–3; Nociceptive/emotional 1–5, Likert rating scale using a faces pictorial display; Functional: Scored as 3 easily, 2 with difficulty, 1 not at all; Cognitive: Performance variability tolerance factor (TF) is applied. Participants not included in subsequent analysis if baseline scores are equal to or less than the TF *PACU* post-anaesthesia care unit, *POD1* postoperative day 1, *POD3* postoperative day 3, *SpO2* blood oxygen saturation, *PONV* postoperative nausea and vomiting, *DOB* date of birth, *ADL* activity of daily living

### Definitions

The IAP will be recorded as read from the gas insufflator device. In the intervention group the ‘individualised IAP’ is defined as the highest IAP needed to obtain and maintain an adequate workspace until completion of surgery. The IAV is calculated by linear interpolation from the patient’s IAP/IAV curve obtained during initial pneumoperitoneum insufflation matching to the IAP at which surgery is performed.

‘Adequate’ workspace is defined as the intra-abdominal workspace sufficient to perform the surgical procedure with no need for corrective manoeuvres (i.e. IAP increase) as judged by the attending surgeon, who remains blinded for the actual IAP. Consequently, ‘inadequate’ workspace is defined as an intra-abdominal workspace insufficient to perform the surgical procedure with the need for corrective manoeuvres (i.e. IAP increase).

Definitions of the various postoperative complications recorded are in accordance with the current European standards for perioperative outcomes (Table 3) [32]. Severity of postoperative complications is evaluated using Clavien-Dindo grading (Table 4) [33].

**Table 3 Tab3:** Classification of postoperative complications

1. Acute kidney damage	
2. Acute respiratory distress syndrome (ARDS)	
3. Suture dehiscence	
4. Arrhythmia	
5. Cardiac arrest	
6. Cardiogenic pulmonary edema	
7. Deep vein thrombosis	
8. Postoperative delirium	
9. Gastrointestinal bleeding	
10. Infection	
11. Bacteraemia	
12. Myocardial infarction	
13. Myocardial injury after non-cardiac surgery	
14. Pneumonia	
15. Paralytic ileus	
16. Postoperative haemorrhage	
17. Pulmonary embolism	
18. Cerebrovascular accident	
19. Infection of surgical wound (superficial)	
20. Infection of surgical wound (deep)	
21. Infection of surgical (organ) wound	
22. Urinary tract infection	
Postoperative pulmonary complications:	
1. Respiratory infection	
2. Respiratory failure	
3. Pleural effusion	
4. Atelectasis	
5. Pneumothorax	
6. Bronchospasm	
7. Pneumonia due to aspiration

**Table 4 Tab4:** Severity grade by Clavien-Dindo definition

Grade I	Any deviation from the normal postoperative course without the need for pharmacological treatment or surgical, endoscopic or radiological interventions Allowed therapeutic regimens are drugs as antiemetic, antipyretics, analgesics, diuretics and electrolytes and physiotherapy. This grade also includes wound infections opened at the bedside
Grade II	Requiring pharmacological treatment with drugs other than such allowed for Grade I complications Blood transfusions and total parenteral nutrition are also included
Grade III	Requiring surgical, endoscopic or radiological intervention
- IIIa	Intervention not under general anaesthesia
- IIIb	Intervention under general anaesthesia
Grade IV	Life-threatening complication (including CNS complications)^a^ requiring IC/ICU management
- IVa	Single organ dysfunction (including dialysis)
- IVb	Multiorgan dysfunction
Grade V	Death of a patient
Suffix ’d’	If the patient suffers from a complication at the time of discharge, the suffix ’d’ (for ‘disability’) is added to the respective grade of complication. This label indicates the need for a follow-up to fully evaluate the complication

^a^Brain haemorrhage, ischaemic stroke, subarrachnoidal bleeding, but excluding transient ischaemic attacks (TIAs)

*IC* intermediate care, *ICU* intensive care unit, *CNS* central nervous system

Respiratory system driving pressure (ΔP_rs_) is calculated by subtracting positive end-expiratory pressure (PEEP) from Pressure plateau (Pplat) [34]. Perioperative safety issues are recorded during the surgery and are related to involuntary patient movements, and defined as diaphragm or abdominal wall contractions or spontaneous breathing efforts or coughing during anaesthesia.

Hospital LOS is defined as hospital discharge date minus hospital admission date.

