## Background

Compared to open surgery, laparoscopic surgery generally results in better outcomes [1, 2]. Compared to open abdominal surgery, a laparoscopic approach during abdominal surgery is associated with less blood loss and fewer needs for blood transfusions [3, 4], faster recovery of bowel function and oral intake resumption [5, 6], fewer analgesic requirements [6, 7] and a shorter length of hospital stay (LOS) [3–8]. Patient-reported outcomes (PROs) are new tools for testing quality of recovery in the postoperative setting, and the Post-operative Quality of Recovery Scale (PQRS) has been successfully tested in previous studies.

A high intraoperative intra-abdominal pressure (IAP) is clearly associated with perioperative morbidity [9–14]. While guidelines for laparoscopic abdominal surgery recommend the lowest possible IAP at which the surgeon has adequate workspace rather than using a predetermined level [15, 16], it remains common practice to use a standard IAP level throughout the surgical procedure, usually between 12 and 15 mmHg and sometimes even higher depending on surgical indication [17]. Interestingly, while the surgical condition depends mainly on the intra-abdominal volume (IAV) and the workspace obtained at a given IAP, the focus during pneumoperitoneum insufflation remains with the applied IAP [18].

Several factors improve the relation between IAP and the obtained surgical workspace, including patient positioning [19], use of neuromuscular blockade [20, 21] and prestretching of the abdominal wall [22]. The previous pivotal and feasibility study, Individualized Pneumoperitoneum Pressure in Colorectal Laparoscopic Surgery I (IPPCollapse-I), showed that combining all these factors with individualised IAP titration resulted in an acceptable workspace at 8 mmHg IAP in 61 out of 78 patients (78%) [23]. The IPPCollapse-II study presented here tests the hypothesis that this individualised pneumoperitoneum pressure strategy improves recovery of PQRS score when compared to a conventional strategy that uses a fixed pneumoperitoneum pressure approach in patients undergoing scheduled colorectal laparoscopic surgical intervention.

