### Individualised pneumoperitoneum pressure strategy

The multifaceted individualised pneumoperitoneum strategy consists of the following elements, which will be performed in the same order in all patients in the intervention group: (1) patient position is modified to increase the anteroposterior intra-abdominal space by correcting lumbar lordosis; (2) patients receive deep neuromuscular blockade throughout surgery to maintain a TOF of 0 and a post-tetanic count (PTC) between 1 and 5; (3) the abdominal wall and muscles are prestretched by maintaining an IAP of 15 mmHg for 5 min during the first CO_2_ gas insufflation and insertion of trocars (to achieve this, the CO_2_ gas insufflator will be initially set at 15 mmHg with a flow rate of 3 L∙min^− 1^); and (4) individualised IAP titration is used when the patient is placed in the surgical position (0–30° Trendelenburg); for this, the flow rate is increased to 30 L∙min^− 1^ and the IAP is decreased from 15 to 12 mmHg, and thereafter stepwise to 11, 10, 9 and finally 8 mmHg as long as the attending surgeon keeps an ‘adequate’ workspace. As in the standard pneumoperitoneum pressure group, surgeons can request an IAP increase up to 15 mmHg, which will be performed likewise. Of note, a pressure increment can be requested by the surgeon at all times in both study arms, where it always follows a similar approach; the previous feasibility study showed that an IAP increase was requested only one time in one-fifth of the patients and never twice [23].

Neuromuscular blockade pharmacological reversion at the end of surgery, before tracheal extubation, is achieved with sugammadex 4 mg∙kg^− 1^.

For clarity, the elements of the two group strategies are summarised in Table 1.

**Table 1 Tab1:** Intervention sequence

Standard pneumoperitoneum pressure strategy (SPP group)	Individualised pneumoperitoneum pressure strategy (IPP group)
1. Trendelenburg (0–30°) placement	1. Trendelenburg (0–30°) + ‘modified lithotomy position’, with flexed hips (between 45 and 90°) and legs raised in padded supports to increase anteroposterior intra-abdominal space
2. Moderate neuromuscular blockade throughout surgery (TOF between 2 and 4)	2. Deep neuromuscular blockade throughout surgery (TOF of 0 and a PTC between 1 and 5)

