### Data to be collected

Before anaesthesia demographic data will be collected including age (years), gender, body height (centimetres) and body weight (kilograms), BMI (kilograms per metre squared), ASA physical status score, comorbidities, number of previous abdominal surgeries and number of previous laparoscopic surgeries and PQRS score.

During anaesthesia the following data will be obtained: levels of IAPs at which surgery is performed (mmHg) in both groups; proportion of patients who needed a pressure increment to achieve acceptable surgical workspace; IAV at start of pneumoperitoneum (litres); coughing and spontaneous movements (yes/no); type of surgery and oncologic status; duration of surgery (minutes); duration of anaesthesia (minutes); proportion of patients who needed conversion from laparoscopic to open surgery and the reason for it (only if applicable); ventilation data including PEEP, plateau pressure and respiratory driving pressure (ΔP_rs_) (all in centimetres of H_2_O pressure) before pneumoperitoneum generation and during initial IAP titration until a stable level of IAP is reached in both groups; type and dose of neuromuscular blocking agent (milligrams); type and dose of neuromuscular blocking reversal agent (milligrams); total opioid requirement during the first 24 h if used (milligrams); and PDR_ICG_ in the stable pneumoperitoneum phase.

Directly after anaesthesia, in the PACU the following will be obtained: PQRS score at 15 and 40 min after PACU admission and on POD1 and POD3; PQRS score in the morning and peripheral venous blood samples for determination levels of biomarkers.

On all postoperative days until hospital discharge and at day 28 the occurrence of postoperative complications and location will be noted.

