### Analysis plan

The statistical analysis plan (SAP) is specified before enrolment of the first patient. In the absence of studies assessing differences in recovery, based on intraoperative IAP management during laparoscopic colorectal surgery, we performed the sample size calculation assuming an odds ratio of 2.65 (equivalent to a difference of 0.5 unit in the logit scale) between groups in the recovery of physiologic PQRS score. It was estimated that a sample size of 170 patients is required to achieve 80% power at a significance level of alpha = 0.05. All reasons for dropouts, expected to be as low as 10%, will be collected and reported. Conversion to open surgery was the main reason for dropouts in the previous study. We will recruit a total of 190 patients to compensate for potential losses.

All analyses will be performed with R software (R Foundation for Statistical Computing, Vienna, Austria). Data will be expressed as the mean (standard deviation, SD) or median (interquartile range, IQR) for continuous variables depending on their distribution (normality will be checked with the Shapiro-Wilks test) and by counts and proportions for categorical variables. The 95% confidence intervals will be calculated for each of the estimated percentiles. The statistical significance level will be set at *P* < 0.05.

The analysis of the primary endpoint follows the intention-to-treat principle. The difference between the recovery PQRS score between groups, the primary outcome on POD1, will be assessed by mixed ordinal logistic regression introducing the patient as random factor, and age, weight, BMI and sex as covariables. The differences in Clavien-Dindo grading of postoperative complications will be assessed by ordinal regression.

For IAV calculation the relationship between IAP and the insufflated volume of CO_2_ will be determined for each patient during initial pneumoperitoneum insufflation. The relationship between IAP and IAV was analysed by linear interpolation from the individual IAP/IAV curves to determine the actual IAV at which surgery is performed. The IAP before CO_2_ gas insufflation was considered the basal IAP or IAP at volume zero, and it was estimated by fitting multiadaptive linear regression splines to the IAV and IAP relationship.

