## Discussion

This study is the first randomised clinical study that tests the hypothesis that an individualised pneumoperitoneum pressure strategy focusing on using the lowest possible IAP, compared to a conventional pneumoperitoneum pressure strategy, improves recovery after laparoscopic colorectal surgery. This study uses the PQRS as well as the occurrence of postoperative complications until postoperative day 28 and also hospital LOS. Furthermore, we assess process-related outcomes like IAP and IAV during pneumoperitoneum and associated ventilator parameters. A strong multidisciplinary commitment between members of the perioperative team, consisting of surgeons and anaesthesiologists, makes this complex study feasible.

The IPPCollapse-II study has several strengths. Its prospective design will allow high accuracy of data to be collected, and its sample size allows us to draw valid conclusions. Selection of PROs as the primary outcome of this study facilitates the translation into clinical practice, since these outcomes are readily and easily perceivable by both patients and healthcare providers. To the best of our knowledge, this is the first multicentre randomised clinical study evaluating the clinical effect of a tailored IAP management. The surgeon will remain blinded for the IAP, allowing us to titrate the IAP to the lowest possible level, i.e. the level at which surgeons have adequate workspace. Furthermore, we aim to describe the relationship between the IAP and actual IAV at which surgery is performed. This could lead, on the one hand, to gathering evidence towards establishing a volume threshold (e.g. the actual workspace) for colorectal laparoscopic surgery to replace the standard pressure threshold, and on the other, to describing the abdominal pressure-volume relationship in a first attempt to achieve something similar to our understanding of lung dynamics during ventilation. Additionally, we directly link the respiratory system and abdomen by assessing the IAP and respiratory driving pressure relationship. This could bring us a step further in achieving protective ventilation in the operating room.

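### Intra-abdominal volume read from the initial insufflation curve omits any prestretch gain at 8–12 mmHg in the intervention arm, so it is not the actual working volume

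*Protocol article*

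**What the plan says.** All references are to the protocol article.

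- **Definitions:** IAV is found by linear interpolation on the patient's own pressure–volume curve, "obtained during initial pneumoperitoneum insufflation matching to the IAP at which surgery is performed". One rule serves both arms.
- **Analysis plan:** the relation between intra-abdominal pressure (IAP) and insufflated volume "will be determined for each patient during initial pneumoperitoneum insufflation". The interpolation is then used "to determine the actual IAV at which surgery is performed". IAV is among the continuous variables compared between groups, by linear regression or the Mann-Whitney test.
- **Data to be collected:** the only volume listed is "IAV at start of pneumoperitoneum (litres").
- **Individualised pneumoperitoneum pressure strategy:** "the abdominal wall and muscles are prestretched by maintaining an IAP of 15 mmHg for 5 min" during the first insufflation. Pressure is then lowered to 12 mmHg and stepwise to as low as 8 mmHg.
- **Standard pneumoperitoneum pressure strategy and Table 1:** controls have no prestretch. They are set at 12 mmHg and can be raised to 15 mmHg on request.
- **Background:** "Several factors improve the relation between IAP and the obtained surgical workspace". Positioning, neuromuscular blockade and prestretching are named.
- **Secondary outcomes:** IAV at which surgery could be performed is a process-related secondary outcome.
- **Discussion:** the IAP–IAV description might contribute to "establishing a volume threshold (e.g. the actual workspace) for colorectal laparoscopic surgery to replace the standard pressure threshold".

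**The concern.** The protocol expects prestretching to shift the pressure–volume relation, yet it reads the operating volume from a curve whose relevant points were recorded before that shift could occur. Only the intervention arm is prestretched by design, so the omission differs between arms.

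Two things are at stake. First, an arm difference in IAV would be published that cannot show any of the gain from one element of the tested strategy. On a rising curve, a lower pressure always returns a lower volume for that patient, so the variable partly re-expresses IAP. Second, a volume threshold derived from these values would rest on volumes that may not have been present during surgery.

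**Working it through.** The documents state no figure that could be reproduced here. The check is one of sequence, followed by an illustration of size.

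**Sequence in the intervention arm** (Individualised pneumoperitoneum pressure strategy)

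1. Position is modified.
2. Deep neuromuscular blockade is given.
3. First insufflation takes pressure up to 15 mmHg, where it is held for 5 minutes.
4. Pressure is lowered from 15 to 12 mmHg, then to 11, 10, 9 and 8 mmHg while workspace stays adequate. Surgery follows.

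Pressure cannot be held at 15 mmHg without first passing through 8–12 mmHg. The curve points at 8–12 mmHg therefore belong to the rise, before the hold, whereas the working pressure is reached on the way down, after it. Steps 1 and 2 come before insufflation, so the curve can reflect them. The component that is lost is prestretch.

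**Size (illustration)**

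Inputs, all assumed because the documents give none: recorded volume V at the working pressure, and a proportional prestretch gain g.

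- True volume = V(1 + g)
- Shortfall in litres = V × g
- Shortfall as a share of the true value = g/(1 + g)

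| g | Share of true value | V = 2 L | V = 3 L | V = 4 L |
|---|---|---|---|---|
| 0% | 0% | 0 L | 0 L | 0 L |
| 5% | 0.05/1.05 = 4.8% | 0.10 L | 0.15 L | 0.20 L |
| 10% | 0.10/1.10 = 9.1% | 0.20 L | 0.30 L | 0.40 L |
| 20% | 0.20/1.20 = 16.7% | 0.40 L | 0.60 L | 0.80 L |

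**Effect on the arm contrast**

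Further assumptions: the same linear curve in both arms, zero volume at a basal IAP of 0 mmHg, 3 L at 12 mmHg, intervention operated at 8 mmHg, control at 12 mmHg.

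- Recorded intervention volume = 3 × 8/12 = 2.0 L
- Recorded difference = 2.0 − 3.0 = −1.0 L
- True difference = 2.0(1 + g) − 3.0, which is −0.9, −0.8 and −0.6 L for g = 5, 10 and 20%

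With a basal IAP of 4 mmHg, the recorded intervention volume is 3 × (8 − 4)/(12 − 4) = 1.5 L and the recorded difference is −1.5 L. The true difference at g = 10% is 1.65 − 3.0 = −1.35 L, and at g = 20% it is 1.8 − 3.0 = −1.2 L. The direction is the same.

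**Range of the curve**

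The rule is interpolation only. If a control's initial curve stops at the 12 mmHg setting, a later working pressure of 13–15 mmHg lies beyond it. The article does not state the highest pressure recorded on the control curve.

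**Position when the curve is taken**

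Table 1 puts Trendelenburg at step 1 in both arms. The text puts it at step 1 for controls, but for the intervention arm it mentions the Trendelenburg surgical position only at step 4, after insufflation. On the text alone, the two arms' curves could come from different positions, and the Background names position as a factor in the relation.

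**The case against.** Several objections have force.

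- **Only one component is lost.** A reader might infer that the IAV rule misses the intervention's whole effect. The documents do not support that. Modified positioning and deep blockade come before insufflation in the stated order, so two of the three factors in the Background can already be in the curve.
- **The timing is partly inferred.** The hold takes place during first insufflation, and the article does not say whether readings during it enter the curve. The inference is firm at 8–12 mmHg and weak near 15 mmHg, which matters for intervention patients whose pressure is later raised.
- **An error confined to the intervention arm is not shown.** Prestretch is confined to that arm. The documents do not say whether sustained 12 mmHg leaves the control relation unchanged, and controls may have their own problem above 12 mmHg.
- **Impossible interpolation in controls is too strong.** Because the top of the control curve is not given, this is a possibility only.
- **The positional discrepancy may be one of wording.** Step 4 can be read as stating a condition and not a later placement.
- **The consequence is limited.** IAV is one of several process-related secondary outcomes, and the volume threshold is offered tentatively.

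These objections narrow the point but do not remove it. At the usual working pressures the rule still cannot register a prestretch gain, and the label of actual volume still claims more than the measurement gives. The article condenses a fuller protocol, so a volume after prestretch may be recorded elsewhere. The article's own rule, however, uses the initial curve.

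**Conclusion.** The point holds in a limited form. For working pressures of 8–12 mmHg, IAV interpolated from the initial curve omits any prestretch gain in the intervention arm. If prestretching acts as the Background expects, the arm comparison understates intervention-arm working volume, and the value is not the actual volume at which surgery is performed.

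The documents support the direction but give no size. The range of 4.8–16.7%, or 0.1–0.8 L across readings of 2–4 L, follows wholly from assumed gains of 5–20% and should not be read as an estimate. With no gain there is no bias.

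The consequence is limited to the IAV outcome and the pressure–volume aim in the Discussion. The primary recovery outcome does not use IAV. The change is worth making because it is cheap and the mislabelled quantity is a planned between-arm outcome.

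**What to change.** 1. In Definitions and the Analysis plan, define and report the variable as the volume predicted from the initial insufflation curve at the working IAP. Remove the description of it as actual IAV.
2. If the insufflator already records a volume after prestretch at the stable working pressure, use that recorded working-pressure volume in both arms. Otherwise, do not base a volume threshold on the interpolated values.
3. State with the result that the arm difference excludes any prestretch gain. Comparing the arms at common pressures on the initial curve would not cure this, because those points also precede the hold.
4. Treat IAV as not estimable, and do not extrapolate, where the working IAP exceeds the highest pressure on that patient's curve. Report how many patients this affects in each arm.
5. Reconcile the text of the individualised strategy with Table 1 on when Trendelenburg is applied relative to the recording of the curve.

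The cost is wording in the definition and the analysis, with no new patients or procedures. The trial gives up a claim about actual working volume that its measurement does not support, and some patients may have no IAV value.
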